#### RETROSPECTIVE ANALYSIS OF ELECTRONIC HEALTH RECORDS:

We will also collect contact information, demographics, provider information, emergency contacts, breast imaging/pathology results, lab results, family history, reproductive history, clinical vitals (e.g., height, weight, BP), clinic encounters, insurance information, allergies, other breast cancer risk factors, medications, clinical notes, and clinical data related to other chronic diseases (such as cardiovascular disease and diabetes). We will assess referral and uptake of genetic counseling and genetic testing.

#### Chart Review of Electronic Health Records:

We will request a waiver of consent in order to collect similar EHR data on ACN patients who have not consented to enroll in the study protocol in order to identify potentially eligible women for recruitment. We will also use this data to assess the extent and quality of family history data in the EHR as well as other factors related to breast cancer genetic testing.

#### Recruitment:

Potential patient participants will be recruited from several different sources: KYRAS Parent Study (AAAO-1761), CUMC/NYP electronic health records (EHR), AVON mammography clinic, and from the community and clinics:

#### RECRUITMENT FROM THE KYRAS PARENT STUDY (IRB-AAAO1761), SISTER STUDY (IRB-AAAP4151), and investigator's other study (AAAJ9559)

Women that meet the eligibility criteria and gave permission for future research contact will be identified from KYRAS survey database (IRB-AAAO1761). They will be approached either in-person, via mail, via email, or via phone and study recruitment information will be given to them. If they are interested, they will be invited to participate in this study.

Potentially eligible patients identified through these study's EHR reviews/TRAC requests will also be noted, and their providers will be recruited. If these providers consent, we will send these patients initial contact messages and approach them if they do not opt out.

#### IN-PERSON RECRUITMENT IN CLINICS:

With the permission of the clinic's medical director or practice administrator, a member of the research team will wait in an area of the clinic designated by clinic staff with the Patient Flyer. Patients will be free to approach the team member for more information about the study. We will not approach patients ourselves unless they give permission to do so after their provider has introduced the study to them.

#### COMMUNITY RECRUITMENT

Recruitment flyers with eligibility criteria will be posted around the medical center campus, in the community, and online. Potential subjects will be directed to contact the study personnel through either phone or email or to the online pre-screener. We will also post recruitment flyers on the internet, using websites and platforms such as Instagram and facebook.

#### RECRUITMENT FROM AVON MAMMOGRAPHY CLINIC:

Our partner study (IRB: AAAP4151) will be recruiting patients from the AVON clinic. If a respondent to this questionnaire is found to be eligible for this research study, we will look to recruit her provider. Once her provider has consented, we will send the patient the initial contact message. If the patient doesn't opt out, she will be approached via phone, email, or in-person, and if interested, will be invited to participate in this study.

#### RECRUITMENT FROM ELECTRONIC HEALTH RECORDS AND SCHEDULING SYSTEMS:

Once a provider has consented, we will monitor the clinical scheduling systems for potentially eligible patients. These patients will be sent the "Initial Contact Message," and if they do not opt out, will be approached to participate in the study.

As only approximately 5% of the general population will be eligible for genetic testing, we will request TRAC requests in order to build a list of patients who are likely to be eligible for genetic counseling and, therefore, this study. We will use this list as a starting point from which to pre-screen patients. Additionally, if patients are identified as likely to be eligible for genetic counseling, and we do not have their providers enrolled, we will recruit their provider as well.

We will collect contact information, demographics (for example, age, race, ethnicity, religion), provider information, emergency contacts, breast imaging/pathology results, lab results, family history, reproductive history, clinical vitals (e.g., height, weight, BP), clinic encounters (both past and scheduled), insurance information, allergies, other breast cancer risk factors, medications, clinical notes, and clinical data related to other chronic diseases (such as cardiovascular disease and diabetes).

We will also use OMPOP/ATLAS data to identify patients who are at an increased likelihood of being eligible for the study. Our goal is to predict breast cancer among the patients who have not yet been diagnosed of breast cancer and to prioritize the recruitment of these high-risk patients for the trial for cancer prevention because it is more likely that they will have a family history of breast/ovarian cancer. With the population EHR data from the institution, we can apply machine learning to build a prediction model to effectively identify the patients at high risk of breast cancer and, therefore, likely to be eligible for genetic testing and the study. We will be running the model for large-scale analysis, and we need a full population data in order to train our model on the population in its entirety for generalization. All patients in the database are candidates for the study, and we will use demographics (for example, age, race, ethnicity, religion), provider information, emergency contacts, breast imaging/pathology results, lab results, family history, reproductive history, clinical vitals (e.g., height, weight, BP), clinic encounters (both past and scheduled), insurance information, allergies, other breast cancer risk factors, medications, clinical notes, and clinical data related to other chronic diseases (such as cardiovascular disease and diabetes). These data will be used to phenotype and define a cohort of non-diagnosed, potentially high-risk patients as well as a cohort of breast cancer patients. The cohorts will then be used to develop and evaluate the prediction model. We require the data in an OMOP common data model for reproducibility of the model. For research purposes, we intend to build a prediction model based on the population data at our institution and also to reproduce and validate the model at external institutions who are collaborators in the OHDSI network using the OMOP common data model. OHDSI (Observational Health Data Sciences and Informatics) is an international collaborative research network that established a common data model (OMOP) to allow systemic analysis of observational databases. Only the algorithm will be shared to be reproduced and to be validated by external institutions with their own data in OMOP common data model, and our institution's data will not be shared. We will also not be using data from other institutions. We also require the scheduling data to check whether high-risk patients have upcoming appointments with a study provider. We are only able to contact the patients with a consented provider, so we will first identify the high-risk patients using the model, and will prioritize the recruitment to those who have an appointment scheduled with a consented provider. All patients who are not referred by their provider will continue to be sent the Initial Contact Message two weeks prior to being recruited. Patients will continue to be prescreened using our pre-screener for study recruitment.

## RECRUITMENT PRIORITIZATION USING EMERGENCY CONTACT INFORMATION

Documentation of family history of breast or ovarian cancer in the EHR is commonly underreported. In order to obtain family history information so we can further prioritize our recruitment lists, we will utilize the method (RIFTEHR) developed by [name] and [name] (AAAO4154) to infer the presence of a family history using emergency

contact linkages in the EHR. Our team will use RIFTEHR to flag patients whose emergency contacts have a history of breast or ovarian cancer and then prioritize reaching out to these patients. The members of the research team who contact patients will not have access to any information on the emergency contacts. They will only have a proband-level six-point scale estimation or a proband-level flag indicating a higher likelihood of a family history. We may also infer Ashkenazi Jewish ancestry using the method developed, which is an important factor included in the six-point scale estimation to indicate eligibility for BRCA genetic testing. This information, specifically a scoring from 0-6, will be the only information derived from this method that will be shown to recruiters to be used to prioritize our recruitment lists. Patients will still be sent the Initial Contact Message and will complete our family history pre-screener to determine eligibility before enrolling.

#### **FOR PATIENTS WHO ARE IDENTIFIED THROUGH THE ELECTRONIC HEALTH RECORDS/SCHEDULING SYSTEMS OR AVON MAMMOGRAPHY CLINIC:**

We will first contact the potential subject's treating physician or clinic director and request that the treating physician/clinic director sign the template of the "Initial Contact Message" that will be sent to the patient to introduce them to the study. Some providers will be asked to consent to this in their consent form.

If the provider/director signs off or consents, a signed letter or email will be sent to the patient with a brief overview of the study and request for permission to contact her for recruitment. The letter requests for patients to opt-out within two weeks if they do not wish to be contacted by the research team.

#### **PATIENTS WHO ARE REFERRED TO THE STUDY BY THEIR PROVIDER:**

If a provider introduces the study and the patient gives permission for us to contact them, we will also contact by phone or email.

### **SCREENING & CONSENT**

#### **Patients**

When a potential human subject has been identified, the research staff will use a short script that briefly explains the study and eligibility criteria. If interested, we will continue to detail all the steps of the study. We will then confirm the eligibility criteria. To assess for genetic counseling eligibility, we will use the Six-Point Scale, which has been adapted to reflect U.S. Preventative Services Task Force (USPSTF) guidelines and is an efficient tool developed in a population of ethnically diverse low-income women to determine eligibility for BRCA genetic testing.

If the participant meets study eligibility, they will be given the option to provide their informed consent over the phone, in-person, or online through Qualtrics. If consent is provided over the phone, the research staff will discuss the informed consent form fully with the participant and verbal consent will be obtained. A copy of the informed consent form will be sent to the participant. Participants who are consented in-person will be presented with the same consent forms, and their signatures will be obtained. If consented online, we will attempt to reach participants to review their consents; they will have the option of saving a copy of the consent directly from Qualtrics.

Potential patient participants will be encouraged to ask questions and their questions will be answered until the potential participants are satisfied. The voluntary nature of the study will be emphasized as well as the right to ask questions and withdraw at any time.

### **Primary Care Providers**

Potential PCP participants will be recruited from the clinics. They will be approached either in person, via mail, via email, or via phone. PCP recruitment flyers will also be posted at the randomization sites. Some sites may distribute a description of the study in their internal newsletter.

Providers will be given the option to review the consent form online through Qualtrics, which will record the provider's consent to participate. The provider will also be given the option to schedule a time to complete a verbal consent over the phone or an in-person appointment where written consent may be documented. For PCP participants consented by phone, the research staff will discuss the informed consent form fully with the provider and verbal consent will be obtained. Providers who are consented in-person will be presented with the same consent forms, and their signatures will be obtained. Potential PCP participants will be encouraged to ask questions and it will be explained that they can withdraw at any time.

In addition, the providers in the intervention arm will receive a provider alert ("BNAV Provider Email Alert") through a secure health message from the EHR and an email from the research staff which will include some of the patients' health information (PCP Action Plan) collected through this protocol (e.g. family history). The email and the alert will direct the provider to the Breast Cancer Navigation Tool (BNAV) which is intended for primary care providers. If the provider has not yet consented when accessing the BNAV tool, they will be presented with the option to consent online through Qualtrics. Provider participants are recruited because they are involved in the clinical encounter and care of the patients who are enrolled in the study.

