**Procedures:**

Primary Care Providers (PCPs):

Potential PCP participants will be recruited from the CUMC/NYP Ambulatory Care Network (ACN) clinics and Columbia Doctors practices.

PCPs will be approached either in person, via mail, via email, or via phone. PCP recruitment flyers will also be posted at the clinics. The PCP's informed consent will be obtained by the research staff listed in the personnel section.

Eligibility criteria for PCPs include:

1) Primary care providers, such as attending physicians, residents, nurse practitioners, physician assistants, and midwives, who see patients at CUMC/NYP ACN clinics or a Columbia Doctors practice

2) Able to provide informed consent

After providing informed consent, PCP participants will complete a baseline questionnaire that collects information on their personal and professional characteristics, subjective risk communication confidence, confidence in managing patients with a family history of breast and ovarian cancer, knowledge, attitudes, orientation towards shared decision making, subjective norms, perceived behavioral control, and intention to refer high-risk patients to genetic testing. Primary care providers will be randomized to either the intervention or control arm.

PCPs in the intervention arm will then be given the Breast Cancer Risk Navigation Tool (BNAV), a web-based provider clinical decision support tool

(<https://kyras.dbmi.columbia.edu/bnav/>), and will be asked to interact with the tool prior to the next clinical encounter with their participating patients. Through BNAV, the PCP will be able to access a patient's individualized risk profile, including family pedigree, and an educational module on genetic testing. The PCP will also be sent a copy of their patient's risk assessment information (BNAV PCP Action Plan) through email and a secure health message (SHM). The BNAV website will include a list of participating patients who are randomized to receive the intervention. The PCP will also be able to view a BNAV notice within the electronic health record (EHR) in iNYP, which includes the patient's personalized breast cancer risk profile and family pedigree.

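### Intervention-arm providers can be sent the alert and Action Plan before they consent or give baseline data, against the protocol's own order and with no control-arm counterpart

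*Protocol*

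**What the plan says.** **Procedures, Primary Care Providers (PCPs).** The sequence opens with "After providing informed consent, PCP participants will complete a baseline questionnaire". That questionnaire covers, among other things, knowledge, attitudes and intention to refer. The next step is "Primary care providers will be randomized to either the intervention or control arm", and intervention providers are then given BNAV. The Action Plan is listed among what they receive: "The PCP will also be sent a copy of their patient's risk assessment information (BNAV PCP Action Plan) through email" and by secure health message. Control providers get neither an Action Plan nor a populated BNAV patient table. They can see only the BNAV notice in the health record. A second provider survey follows six months after baseline.

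**Screening & Consent, Primary Care Providers.** Here "the providers in the intervention arm will receive a provider alert" by secure message, together with "an email from the research staff which will include some of the patients' health information (PCP Action Plan"). Both messages direct the provider to BNAV. The section continues: "If the provider has not yet consented when accessing the BNAV tool, they will be presented with the option to consent online through Qualtrics".

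**Recruitment.** For patients found through health records and scheduling systems, the protocol says: "We are only able to contact the patients with a consented provider". In the Patients part of Procedures, however, a woman may refer herself, and her provider is recruited afterwards if not already enrolled.

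**The concern.** The provider is the unit of randomisation, and each patient takes her provider's arm. The Procedures section has providers join before they know their arm. The Screening & Consent section has some intervention providers decide whether to join after they have been allocated and have received patient-specific material. No such step is described for control providers.

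Two things are at stake. The first is the provider baseline: for a late consenter it is taken after exposure to at least the Action Plan. The second is the comparability of the arms, if joining the trial after the alert decides whether a provider's patients are counted. The first follows directly from the text. The second depends on a rule that the protocol does not give.

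**Working it through.** The point concerns the order of events, and no figure in the protocol measures it. The stated power (above 90% for 5% against 30%, with 95 × 0.80 = 76 patients per arm) reproduces at 98.7% before any allowance for clustering. That result has no bearing on when providers enter.

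**Step 1. The two sequences side by side.**

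| | Procedures | Screening & Consent |
|---|---|---|
| 1 | Consent | In the intervention arm |
| 2 | Baseline questionnaire | Alert and Action Plan sent |
| 3 | Randomisation | Provider reaches BNAV |
| 4 | BNAV and Action Plan (intervention) | Consent offered if not yet given |

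In Procedures, the place of randomisation after baseline is read from the order of the text, while the place of consent before baseline is explicit. A provider who follows that column cannot be both in the intervention arm and unconsented. The right-hand column provides for exactly that provider, so the two sections cannot both be followed.

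**Step 2. Is there a control-arm equivalent?** Control providers receive no Action Plan. They can view the health-record notice, but no consent offer is attached to it. Late recruitment of a provider can happen in either arm. A consent offer triggered by the intervention itself is described in one arm only.

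**Step 3. Effect on the provider baseline.** Let B be the true pre-exposure score, d the shift already caused by exposure, and F the six-month score. Measured change = F − (B + d) = (F − B) − d. If exposure raises scores (d > 0), change is understated by d for each late consenter. The six-month survey is timed from this baseline, so its clock also starts after exposure. A comparison of F alone, without baseline, would not carry this error.

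**Step 4. Effect on the primary endpoint, only if patients are excluded.** Let f be the share of intervention patients whose alerted provider never consents, u their uptake, and 30% (the planned intervention rate) the uptake of the rest. The rate with everyone kept is (1 − f) × 30% + f × u. Dropping these patients gives 30%, a rise of f × (30% − u).

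- Assumed f = 10%, u = 10%: 0.9 × 30% + 0.1 × 10% = 28%, a rise of 2 points.
- Assumed f = 10%, u = 5% (the planned control rate): 0.9 × 30% + 0.1 × 5% = 27.5%, a rise of 2.5 points.
- Assumed f = 10%, u = 30%: no rise.
- If patients are kept as allocated: no rise, whatever f is.

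The protocol gives neither f nor u. These lines show how the effect would work and are not an estimate of it.

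**The case against.** Several arguments on the other side hold and limit the point.

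- **Selection on the primary endpoint is not established.** A reader might infer that reluctant intervention clusters drop out and inflate the result. No section says so. Patients consent for themselves, and uptake is taken from the health record and scheduling systems, which does not depend on provider consent. The alert carries patient information already collected under the protocol, which suggests that these women are already enrolled. If they are analysed as allocated, a provider's refusal removes nobody. What remains is that the protocol does not say which rule applies.
- **The baseline error need not favour the intervention.** It might be read as a second bias in the intervention's favour. Step 3 points the other way.
- **BNAV itself may not be seen before consent.** The prompt could be a gate in front of all content. That would not protect the baseline, because the Action Plan has by then been sent by email and secure message.
- **The rule that patients are contacted only when their provider has consented belongs to the health-record route.** With self-referral, a patient can legitimately be identified before her provider is enrolled. That rule therefore does not contradict the late-consent sentence outright. The direct conflict is with the Procedures section.
- **The aims are patient-level.** Counselling uptake, decisional conflict, shared decision-making and informed choice do not rest on the provider baseline questionnaire.
- **Any exclusion effect may be small.** In the illustration it is 2 to 2.5 points against a planned difference of 30 − 5 = 25 points. This is fair, but the 10% share is itself assumed.

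**Conclusion.** The inconsistency is real and should be fixed. As written, the protocol allows consent and baseline to follow allocation and at least one intervention component, in the intervention arm only. For providers who enter this way, the baseline measures are compromised, and change in knowledge, attitudes and intention to refer is probably understated, assuming that exposure raises those scores. An analysis plan cannot recover a pre-exposure measurement that was never taken.

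For the primary endpoint, the conclusion is conditional. If patients of alerted providers who never consent were excluded, the intervention arm would lose its less engaged clusters with nothing to match in the control arm. The protocol neither states nor rules this out, and the size cannot be calculated from it. The documents do not support a claim that the primary comparison is already biased, or that any such bias is beyond repair: analysis as allocated would prevent it.

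**What to change.** Reconcile Procedures with Screening & Consent so that one order applies in both arms: provider consent, baseline questionnaire, randomisation, and only then release of any alert, Action Plan or BNAV access. Say expressly that this also covers providers recruited after a self-referred patient has been identified. A consent prompt at BNAV log-in can stay as a gate for a provider who reaches the site by another route, provided that no content is shown and that baseline and randomisation follow before anything is released.

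Add one sentence on analysis: all randomised providers and their enrolled patients are analysed in the allocated arm, whether or not the provider uses BNAV or later stops.

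The cost is revised wording and an access check on the alert and the log-in. The downside is that the provider component may start later for some patients already enrolled. The protocol gives no figure from which to judge how many.
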